### Study duration

The study will be carried out for a total period of one year (between January 2020 and December 2020).

### Eligibility criteria

Fathers of infants and young children with poor involvement in IYCF in households in Dakshina Kannada District will be selected for this study. Initial assessments of all fathers from selected households (see
*Study population)* will be conducted to assess fathers’ knowledge, attitude and practices towards IYCF (see questionnaire in
*Extended data*
^27^). Fathers with scores in the lower 50
^th^ percentile in the practice domain will be categorized as fathers with poor involvement in IYCF and will be eligible for inclusion in the RCT.

Those fathers who are not available for interventions despite three attempts of contact will be excluded. To promote retention of the participants, visits will be made to them at a convenient time and location. 

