### Intervention procedure

An IYCF improvement module that has been developed as an easy to use flip chart with a blend of pictures and textual materials has been produced (IYCF module,
*Extended data*:
^27^), which included the basic aspects of infant and child nutrition and feeding: (i) assisting in feeding; (ii) changing diapers; (iii) giving a bath to the child; (iv) putting the child to sleep; (v) playing with the child and (vi) taking the child outside the home, (e.g. - for a walk).

The module was developed based on the available literature and brainstorming sessions with the researchers. All the investigators were involved in implementing the brainstorming technique and three investigators (PM, RT and PR) designed the module to the final format. The module will be implemented in the local language (Kannada).

This module will be administered to the intervention group only. The control group will receive regular care at the study centers, which is routinely made available to them whenever they visit health centres or when health workers visit them. This will not affect the ultimate results of the study. The administration of the module to the intervention group will be done monthly for six months. Both groups will be followed up at the end of six months, during which they will be assessed for the level of involvement in IYCF, which is the same method as that of pre-assessment (see questionnaire,
*Extended data*
^27^).

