### Data collection methodology

Necessary permissions are taken from the Head of the Institute and District Health Authorities. Two Research Assistants will be recruited from the field of Social Work, with communication skills and ability to interact with the population using the local language. After their training on implementation of the module, they will visit the study participants for the implementation.

The fathers accompanying the infants will be approached and will be provided with the participant information sheet (
*Extended data*
^27^). Written informed consent will be taken from each of them by the research assistants and they will be allocated to one of the intervention groups and one-to-one interaction for module implementation will be followed as stated above. The assessment at six months will be done by the research assistants for both the groups with respect to knowledge, attitude and involvement (practices) in their IYCF.

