### Data analysis

Results will be expressed as proportions, mean (with standard deviation), median (with interquartile range), using appropriate tables and figures. We will follow intention to treat analysis (ITT). The comparison for the continuous variables will be done using the “t” tests. For comparison across the groups, Chi square tests and Multiple Logistic Regression will be used and p<0.05 will be considered statistically significant.

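### The rule excluding fathers unavailable for the intervention has no stated timing; on its most natural reading it removes randomised fathers from one arm and conflicts with the intention-to-treat analysis

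*Protocol article*

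**What the plan says.** The rule stands in the protocol article under Eligibility criteria: "Those fathers who are not available for interventions despite three attempts of contact will be excluded". The next sentence turns to fathers already in the trial: "To promote retention of the participants, visits will be made to them at a convenient time and location".

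Intervention procedure says who gets the module and how often: "This module will be administered to the intervention group only", and "The administration of the module to the intervention group will be done monthly for six months". For the other arm, "The control group will receive regular care at the study centers, which is routinely made available to them". The shared contact point after baseline is the final assessment: "Both groups will be followed up at the end of six months".

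Data collection methodology gives the order. After consent, "they will be allocated to one of the intervention groups and one-to-one interaction for module implementation will be followed as stated above".

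Data analysis names the analysis principle: "We will follow intention to treat analysis (ITT)".

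The article does not say at what stage the three attempts are counted, gives no matching rule for controls, and does not say whether an excluded father is still assessed at six months or kept in the analysis.

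**The concern.** The rule turns on availability for the intervention, not for the baseline interview or for consent. A control father has no module visit to miss. If the rule operates during the six months of visits, it can therefore take out intervention fathers while comparable control fathers stay in.

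That matters more here than in most trials because the outcome is paternal involvement. A father who cannot be found after three attempts is plausibly one who is also less involved in feeding his child. Taking such fathers out of one arm would raise that arm's mean even if the module did nothing. The trial is unblinded, and the research assistants who deliver the module also carry out the six-month assessment, so blinding gives no protection against selective removal.

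**Working it through.** **Step 1: reading the sections together.** The protocol gives no figure for this rule, so there is none to reproduce. The question is when and on whom the rule acts.

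- Data collection methodology puts consent first, then allocation, then one-to-one module contact. Availability for the module is thus tested by visits that follow allocation.
- Intervention procedure confines those visits to one arm.
- The sentence after the rule concerns retention, which applies to fathers already enrolled.
- Against this, the rule is placed under Eligibility criteria, and Sampling strategy and randomization allocates fathers who have already been found eligible.

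The first three points favour a post-allocation, one-arm rule. The fourth leaves room for a screening rule. The text does not settle it.

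**Step 2: what the rule could do if applied after allocation.** Inputs:

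- Arm size: 60 per arm from the abstract's total of 120, or 30 per arm from the total of 60 under Sample size. The article gives both totals, so both are shown.
- Share dropped from the intervention arm, u: 10% or 20% (assumption). The 20% borrows the size of the non-response allowance under Sample size, which is a general allowance on the whole sample and not a forecast of loss through this rule.
- Correlation r between availability and the six-month practice score: 0.3 or 0.5 (assumption).
- No true effect; outcome in SD units; normal approximation; two-sided 5% test.

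If the least available share u is removed, the mean availability of those who remain is φ(z_u)/(1−u), where z_u is the u-quantile of the standard normal. This is 0.195 for u = 10% and 0.350 for u = 20%.

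Bias = r × φ(z_u)/(1−u), which gives:

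- u = 10%: 0.3 × 0.195 = 0.0585 SD; 0.5 × 0.195 = 0.0975 SD
- u = 20%: 0.3 × 0.350 = 0.105 SD; 0.5 × 0.350 = 0.175 SD (0.17498 before rounding)

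SE = √(1/(n(1−u)) + 1/n), and type I error = P(|Z + bias/SE| > 1.96).

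| Analysed (module v control) | SE | r | Bias (SD) | Type I error |
|---|---|---|---|---|
| 54 v 60 | 0.188 | 0.3 | 0.0585 | 6.1% |
| 54 v 60 | 0.188 | 0.5 | 0.0975 | 8.1% |
| 48 v 60 | 0.194 | 0.3 | 0.105 | 8.4% |
| 48 v 60 | 0.194 | 0.5 | 0.175 | 14.7% |
| 27 v 30 | 0.265 | 0.3 | 0.0585 | 5.6% |
| 27 v 30 | 0.265 | 0.5 | 0.0975 | 6.6% |
| 24 v 30 | 0.274 | 0.3 | 0.105 | 6.7% |
| 24 v 30 | 0.274 | 0.5 | 0.175 | 9.8% |

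**Step 3: a second model as a check.** Let the dropped fathers score g SD below the available ones, so that bias = u × g. With 60 per arm, u = 10% and g = 0.5 give 0.05 SD and a type I error of 5.8%; u = 20% and g = 1.0 give 0.20 SD and 17.8%. With 30 per arm and u = 20%, g = 0.5 gives 6.5% and g = 1.0 gives 11.3%. The order of size is the same.

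**Step 4: after the fix.** If every randomised father stays in his arm and is assessed, the bias from this rule is zero and the type I error returns to 5%.

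**The case against.** A reader might infer that the rule can act only on the intervention arm, and that it cannot be followed together with intention to treat. The document does not support going that far:

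- The sentence is an eligibility criterion, and eligible fathers are allocated afterwards.
- Household visits also take place before allocation, for example to verify identity and the child's age, so three failed contacts could occur at that stage.
- Data collection methodology refers loosely to both arms as intervention groups, so the rule's wording need not mean module visits.
- Exclusion is not expressly exclusion from the analysis. A father might stop receiving visits and still be assessed and analysed in his arm.

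On a screening reading the rule acts before the arms exist, and intention to treat is untouched.

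The size is also open to challenge. Neither the one-arm loss nor the correlation is in the document, the direction of bias is inferred, and the milder inputs move the type I error by only about one percentage point or less. Nothing shows that any father has been dropped this way. The article is also condensed, and the flow diagram held in its extended data is not at hand.

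These points stand as limits on the claim. They do not remove it. The wording about availability for the intervention and the retention sentence beside it point to the post-allocation reading, and staff applying the text literally would drop intervention fathers who miss visits. This is also not a detail left to a fuller document: the article states the rule and states an analysis principle that the rule, so read, would break.

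**Conclusion.** The concern holds in this form: the timing and scope of the three-attempt exclusion are not stated, and the most natural reading is a one-sided exclusion after randomisation that conflicts with the stated analysis principle. It is not shown that the authors intended this or that it has happened.

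If the rule is applied after allocation, the likely direction is in favour of the module, on the inference that unreachable fathers are less involved. Under the assumed 10-20% loss and correlation of 0.3-0.5, the false benefit is about 0.06-0.17 SD. The two-sided type I error is about 6-15% at 60 per arm and 6-10% at 30 per arm. The upper end needs the larger loss, the stronger correlation and the larger sample together. If the rule was a screen before randomisation, none of this bias arises and only the wording needs correcting.

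It should be settled before the six-month assessment. Current status of the study reports recruitment complete and four of the six monthly rounds given, so outcomes on every randomised father could still be sought at that point.

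**What to change.** - State that the three-attempt rule applies only before randomisation.
- After allocation, record missed module sessions as adherence. They are not a reason for exclusion.
- Make the same number of attempts at the six-month assessment in both arms, including fathers who missed module visits and any randomised father already dropped for unavailability.
- Analyse all assessed fathers in the arm to which they were assigned.

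With recruitment finished, the first item cannot change past conduct. Its use now is to make the rule clear; the practical gain comes from the other three.

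The cost is a wording change and some extra assessment attempts by the existing research assistants. Their number depends on how many fathers have been dropped: probably a few, but up to 12 of 60 or 6 of 30 if the assumed 20% loss were real. The estimated effect may come out slightly smaller, because fathers who received little of the module remain in the comparison.

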### Sampling strategy and randomization

The study participants will be identified using multi-stage random sampling technique, wherein from each of the five Taluks of the District equal number of participants will be selected irrespective of their locality (urban or rural). Within each Taluk, one Public health institution and in the area covered by that institution, one ward (an administrative unit) will be selected using lottery technique. List of participants will be obtained from these public health institutions and number of participants from each selected ward will be decided based on probability proportionate to size. In the wards, they will be selected using convenience method till the required sample size gets covered.

Based on the findings from initial assessment at the district for level of knowledge, attitude and practices towards paternal involvement in IYCF, the areas with fathers of infants with poor IYCF practices will be mapped for visits at their households. Selected eligible participants will be allocated to modular intervention and control groups. A simple randomization technique with 1:1 allocation will follow. A lottery technique will be used for randomization, until the needed sample size is reached, with the help of Microsoft Excel software. The principal investigator will generate the sequence for randomization and another author (NK) will enroll the participants according to this sequence. The research assistants will implement the modular intervention.

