### Study design

The study will be a unblinded parallel group RCT. This study will follow the Consolidated Standards of Reporting Trials (CONSORT)
^25,
26^. The study flow according to CONSORT guidelines is depicted in the
*Extended data*
^27^. This study protocol is reported along with Standard Protocol Items: Recommendations for Interventional Trials (SPIRIT) Guidelines
^28^. A completed SPIRIT checklist can be found in the
*Reporting guidelines*
^27^.

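### As written, nothing hides the next assignment from the author who enrols fathers, so selection bias could enter this unblinded trial; the planned unadjusted comparison would not correct for it

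*Protocol article*

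**What the plan says.** All references are to the Protocol article.

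- **Sequence and enrolment** (Sampling strategy and randomization): "The principal investigator will generate the sequence for randomization and another author" "will enroll the participants according to this sequence". Two different people do the two jobs.
- **Method** (same section): "A simple randomization technique with 1:1 allocation will follow". The tool is also named: "A lottery technique will be used for randomization, until the needed sample size is reached, with the help of Microsoft Excel software".
- **Choice of fathers** (same section): "In the wards, they will be selected using convenience method till the required sample size gets covered".
- **Blinding** (Study design): "The study will be a unblinded parallel group RCT".
- **Consent and allocation** (Data collection methodology): "Written informed consent will be taken from each of them by the research assistants and they will be allocated to one of the intervention groups".
- **Analysis** (Data analysis): t tests for continuous variables; chi-square tests and multiple logistic regression for comparisons across groups. No covariates are named.
- **Status** (Current status of the study): recruitment is finished and four of the six monthly rounds have been given.

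**The concern.** Randomization protects the comparison only if the person who brings a father into the trial cannot know which arm he will get. The article describes the procedure in some detail (lottery, Excel, who generates, who enrols), and none of those steps hides the assignment. An enroller who works from the sequence itself would know the next arm.

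Two stated features would make such knowledge usable. Convenience selection leaves the choice of whom to approach to someone's discretion, and the trial is unblinded. A father who seems more cooperative or easier to reach could end up in the module arm more often, and he might well score higher on practice at six months whatever the module does. An unadjusted t or chi-square test would count that difference as effect.

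**Working it through.** **1. The procedure, read step by step.** There is no stated figure to reproduce, because the point concerns procedure.

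- Generation and enrolment are separated. This is a partial safeguard, and it conceals allocation only if the enroller cannot see the list.
- Enrolment is said to follow the sequence. No section mentions sealed envelopes, central allocation or any other barrier between the enroller and the list.
- Convenience selection is described in the paragraph on sampling. The next paragraph moves from the initial assessment to allocating the eligible fathers already selected, which suggests that fathers are chosen and scored before arms exist. But the lottery is said to run until the sample size is reached, which would also fit father-by-father enrolment. The order is unclear.
- Data collection methodology puts consent before allocation. It uses the passive voice, so it does not say who assigns, and it does not say whether the enrolling author already knew the arm.

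**2. What a selection shift would do to the test.**

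Inputs:
- Two-sided level 0.05 (Data analysis), critical value 1.96.
- Number per arm n: 30 from the total of 60 under Sample size, or 60 from the total of 120 in the Abstract. The two totals conflict. That is a separate matter, so both are shown.
- Shift b between arms from selection, in SD of the outcome. This is assumed, because the article gives no figure; the range is 0.1 to 0.3.

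With no true effect, a two-group z-test rejects with probability

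1 − Φ(1.96 − b√(n/2)) + Φ(−1.96 − b√(n/2)).

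For n = 30, √(30/2) = 3.873. At b = 0.2 the product is 0.775, giving 1 − Φ(1.185) + Φ(−2.735) = 0.121. For n = 60, √(60/2) = 5.477. At b = 0.2 the product is 1.095, giving 1 − Φ(0.865) + Φ(−3.055) = 0.195.

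| Assumed shift b (SD) | 30 per arm | 60 per arm |
|---|---|---|
| 0 | 5.0% | 5.0% |
| 0.1 | 6.7% | 8.5% |
| 0.2 | 12.1% | 19.5% |
| 0.3 | 21.3% | 37.6% |

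If 20% of fathers were lost, the 0.2 SD figures would be 10.7% (24 per arm) and 16.5% (48 per arm).

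**3. What is available to correct it.** The practice score is measured in every father before entry, since it decides eligibility (Eligibility criteria), and again at six months by the same method (Intervention procedure). Taluk is known from the sampling. Both can enter the primary model without new data.

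**The case against.** The strongest reply is that lack of concealment is an inference. Enrolling in line with a sequence is compatible with slips or a call to the person who generated it, and a journal article may leave the device to the full protocol. If fathers were sampled and scored before any arm existed, nobody could have matched a father to a slot by choosing whom to approach.

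Much of this stands. A reader might infer that the enroller saw upcoming arms, or that steering took place; the article says neither. A reader might also infer that the research assistants allocate, contradicting the section that names an author. The text says only "they will be allocated to one of the intervention groups", which is compatible with assistants taking consent and an author assigning. That calls for clarification and does not establish a conflict. Nor is simple randomization at fault: an unrestricted 1:1 draw is valid, chance imbalance between Taluks does not bias the test, and blocking would be a preference.

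What does not fall away is that the article goes beyond omitting a detail. It sets out a procedure and ties enrolment to the sequence. Followed as written, nothing keeps the next arm from the enroller, and the unclear order of sampling and allocation does not close the gap.

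**Conclusion.** The point holds as a risk created by the stated procedure. The documents do not show that bias occurred or that the sequence was visible in practice.

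On an assumed shift of 0.1 to 0.3 SD, the false-positive rate of the unadjusted comparison would be about 7–21% with 30 per arm (12% at 0.2 SD) or about 9–38% with 60 per arm (20% at 0.2 SD), against a nominal 5%. These figures rest on the assumed shift, the normal approximation and no loss to follow-up. If allocation was in fact concealed, the expected shift is zero and the rate stays at 5%.

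**What to change.** Recruitment is complete, so the changes concern reporting and analysis.

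1. State who held the sequence and when each assignment was revealed. If it was not concealed, report this as a limitation.
2. Tabulate baseline practice score, child age and Taluk by arm.
3. Make the primary comparison of the six-month practice score a model with arm, baseline practice score and Taluk, in place of the unadjusted t or chi-square test. With four of six rounds given, this can be fixed before the six-month assessment is analysed.
4. Make clear across Sampling strategy and randomization and Data collection methodology who enrols, who takes consent and who assigns, and in what order.
5. For any further enrolment, reveal the arm only after consent and baseline scoring, from a list that the enroller cannot see.

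The cost is some wording and slightly more analysis, with no new data. The downside is that a limitation may have to be admitted. Adjustment removes only differences in what was measured at baseline; steering on cooperativeness or availability would be only partly captured.

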### Intervention procedure

An IYCF improvement module that has been developed as an easy to use flip chart with a blend of pictures and textual materials has been produced (IYCF module,
*Extended data*:
^27^), which included the basic aspects of infant and child nutrition and feeding: (i) assisting in feeding; (ii) changing diapers; (iii) giving a bath to the child; (iv) putting the child to sleep; (v) playing with the child and (vi) taking the child outside the home, (e.g. - for a walk).

The module was developed based on the available literature and brainstorming sessions with the researchers. All the investigators were involved in implementing the brainstorming technique and three investigators (PM, RT and PR) designed the module to the final format. The module will be implemented in the local language (Kannada).

This module will be administered to the intervention group only. The control group will receive regular care at the study centers, which is routinely made available to them whenever they visit health centres or when health workers visit them. This will not affect the ultimate results of the study. The administration of the module to the intervention group will be done monthly for six months. Both groups will be followed up at the end of six months, during which they will be assessed for the level of involvement in IYCF, which is the same method as that of pre-assessment (see questionnaire,
*Extended data*
^27^).

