### Study population

Fathers attending to infants (children aged <1 year) and young children (children aged 12–23 months) in selected households belonging to the geographical areas covered by public health care institutions of Dakshina Kannada District will be included. Households will be identified through records maintained in at public health care institutions. At the time of visit to their houses, their identity will be verified, along with confirmation of the age of their child.

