### Instruments for data collection

Pre-tested, validated, semi-structured proforma will be used both pre- and post-intervention (questionnaire,
*Extended data*
^27^). The instrument will include the demographic details of the participants and Likert scores in these domains: knowledge, attitude and practices (involvement) towards IYCF.

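### Children entered at 18–23 months are past the study's own age range at the six-month assessment, and the planned t tests leave child age as noise: adjust the between-arm comparison for baseline score and child age

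*Protocol article*

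**What the plan says.** The Study population section of the protocol article defines who may enter: "Fathers attending to infants (children aged <1 year) and young children (children aged 12–23 months) in selected households". It adds that identity is verified at the home visit, "along with confirmation of the age of their child". No upper entry age allows for the length of follow-up.

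The Intervention procedure section fixes the outcome time: "Both groups will be followed up at the end of six months, during which they will be assessed for the level of involvement". It says that the method is the one used before the intervention, and the Instruments section confirms that the "proforma will be used both pre- and post-intervention". No version or scoring by child age is described.

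Eligibility rests on a single cut-off over all child ages: fathers in the lower 50th "percentile in the practice domain will be categorized as fathers with poor involvement in IYCF".

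The Outcomes section lists knowledge, attitude and practice scores. The Data analysis section plans t tests for continuous variables, plus chi-square tests and multiple logistic regression, and names no covariates. Randomisation is simple and 1:1, with no stratification stated. The Current status section reports that recruitment is complete and that four monthly rounds have been given, out of six planned.

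**The concern.** The study defines infants and young children as those under 24 months. With a six-month follow-up and entry allowed up to 23 months, the endpoint for some fathers describes involvement with a child older than that definition.

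The module covers feeding help, diaper changes, bathing, settling to sleep, play and outings. What a father does in these tasks plausibly changes between birth and 29 months. If the practice score changes with them, two things are at stake:

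- **Interpretation.** The Outcomes section speaks of improvement achieved by the modules and of change in knowledge and attitude. The Data analysis section does not say whether its t tests are within or between arms. A within-arm change would combine six months of ageing with any module effect.
- **Precision.** An unadjusted t test leaves age-related spread in the error term. With simple randomisation in a small trial, the arms can also differ in child age by chance.

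**Working it through.** **Inputs.** Entry age 0–23 completed months (Study population). Endpoint at six months, same instrument (Intervention procedure; Instruments). Total size 60 in the Sample size section but 120 in the Abstract; that conflict is a separate matter, so both are carried through. The article gives no figure for children leaving the age range, so there is nothing to reproduce.

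**1. Age at the endpoint.** 18 + 6 = 24 and 23 + 6 = 29, so entry at 18–23 months means 24–29 months at assessment. The oldest entry age that stays in range is 17 months (17 + 6 = 23).

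**2. Share affected.** If entry ages are uniform over 24 monthly bands (assumption), 6/24 = 25%, which is 15 of 60 or 30 of 120. More generally, with a proportion q of infants and uniform ages within each band, the share is (1 − q) × 6/12:

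| Infants (q) | Past 23 months at endpoint |
|---|---|
| 100% | 0% |
| 75% | 12.5% |
| 50% | 25% |
| 0% | 50% |

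**3. Is the between-arm comparison biased?** A null trial was simulated (3,000 runs per setting) with child age driving both scores, fathers selected below the median baseline score, and 1:1 allocation. With age explaining 0, 10 or 30% of score variance, the mean unadjusted effect was about 0 and type I error was about 0.045–0.055. There is no bias.

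**4. Chance imbalance.** With a 25% share, the 95% range of the difference between arms is ±1.96 × √(2 × 0.25 × 0.75 / n):
- n = 30 per arm: 1.96 × 0.112 = ±22 points
- n = 60 per arm: 1.96 × 0.079 = ±15 points

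**5. Precision.** In the same simulation, adjusting for age and baseline score together at an age R² of 0.3 cut the standard error from 0.223 to 0.192 (30 per arm) and from 0.159 to 0.136 (60 per arm), about 14%.

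That is a joint gain. If age were the only covariate, the gain in effective sample size would be 1/(1 − R²): 1/0.90 = 1.11 and 1/0.80 = 1.25 for an R² of 0.10 and 0.20. Once baseline score is in the model, age adds less. Under the simulation's structure (age R² = r in both scores, and a correlation of 0.5 between the two scores at a given age), baseline alone explains ((1 + r)/2)² of the variance, and both together explain r + 0.25(1 − r):

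| r | Baseline alone | Both | Extra gain from age |
|---|---|---|---|
| 0.10 | 0.3025 | 0.325 | 0.6975/0.675 = 1.03 |
| 0.20 | 0.36 | 0.40 | 0.64/0.60 = 1.07 |
| 0.30 | 0.4225 | 0.475 | 0.5775/0.525 = 1.10 |

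All values of r are assumptions.

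**The case against.** The strongest reply is that the trial is randomised with a concurrent control arm assessed at the same time by the same method. Ageing acts equally on both arms and cancels in their contrast. This stands, and the simulation agrees. A reader might infer that natural development will be mistaken for a module effect in the trial result; that could happen only if within-arm change were taken as the evidence.

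It can also be said that the age limit is an entry criterion, that nothing requires a child to be under 24 months at the outcome, and that nothing says the module's tasks lose meaning at 24–29 months. This also stands. The issue is how the endpoint is described and interpreted, not a protocol breach.

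Other stronger readings go beyond the text:
- That many children age out: the age distribution is not given.
- That child age determines both eligibility and outcome, or that the cut-off favours fathers of the youngest infants: the questionnaire is not shown, and no passage says so.
- That one cut-off also governs the endpoint: the percentile is stated for eligibility only, and the outcomes are scores.
- That no analysis uses child age: the logistic regression names no covariates, and these may sit in an analysis plan that is not shown. The lack of adjustment is a feature of the t tests only.

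**Conclusion.** The point holds in a limited form. Children entered at 18–23 months are certain to be past the study's own age range at the only outcome assessment. Their share is about 25% under uniform entry ages and anywhere from 0 to 50% depending on the age mix. The randomised comparison remains unbiased.

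What is lost is a clean reading of any within-arm change and some precision, both only if the practice score varies with child age. That is plausible from the module's content but undocumented. The benefit of adding age to a model that already holds baseline score is likely to be below the 11–25% that age alone would suggest. Most of the argument for the change is that it costs almost nothing and can still be fixed before the outcome is seen.

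**What to change.** Before the six-month data are examined, state in the analysis section that:

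1. The t test on practice score is replaced by a between-arm linear model (ANCOVA) of the six-month score, adjusted for baseline practice score and child age in months at entry.
2. Effectiveness is judged on the between-arm contrast. Within-arm change is descriptive only.
3. A sensitivity analysis repeats the model in children aged 17 months or younger at entry, who are all still within range at the endpoint. Report the distribution of child age at entry and at six months.

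**Cost.** No new recruitment or visits, and slightly more analysis work. Age is confirmed at the household visit; check that it was recorded in months, because the Instruments section mentions only the demographic details of participants. The sensitivity analysis uses fewer fathers: under uniform ages 18/24 = 75%, that is 45 of 60 or 90 of 120 before any loss to follow-up. Capping entry age or setting the eligibility cut-off within age bands would have no use now, since recruitment is complete.
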